**Inclusion and exclusion criteria**

The inclusion criteria for the study participants will be women aged 30-60 years residing in the slum area, those who have not been diagnosed with cervical cancer, and those who are not planning to migrate to another place in the next 3 months. The exclusion criteria will be women who are currently pregnant and those who have undergone a hysterectomy.

**Intervention**

Ten participants who had at least passed the SLC will be enrolled as community health workers (CHWs) in the intervention group. Training on cervical cancer will be provided to the CHWs by the principal investigator and a nurse using presentation slides. The training will be for one day (4 hours). CHWs will be mobilized in the intervention group using flip charts and brochures. After a day of receiving the training, CHWs will reach the doors of the participants to provide health education on cervical cancer, which will be monitored once by the principal investigator. CHWS will visit the participants just once for an education session, which will take 15 minutes for each participant. CHWs will distribute brochures to every participant in the intervention group. All of the participants of the intervention group will receive the intervention. In the control group, posters will be displayed in two different locations after the baseline study.

**Outcomes**

The primary outcome will be a change in knowledge of cervical cancer. Secondary outcomes include changes in cervical cancer screening uptake, perceived susceptibility, perceived severity, and behavioral intention related to cervical cancer from baseline to midterm and endline assessments.

**Benefits to participants and handling of possible risks**

The study will be done in such a way that no harmful effects are created for the participants. The participants will benefit from the health educational intervention, which focuses on cervical cancer screening behavior and knowledge related to the prevention and control of cervical cancer.

**Ethical considerations**

The ethical approval will be taken from the Institutional Review Committee (IRC), Pokhara University. Written consent from the participants will be obtained before the study begins. Data collection will be conducted in the Nepali language to ensure participants’ understanding. Withdrawal will be accepted at any time during data collection. Anonymity will be maintained by keeping code numbers in questionnaires. Confidentiality will be maintained by using the obtained information for the study only.

**Data Analysis**

Statistical Package for Social Sciences (SPSS v22) will be used to store and analyze quantitative data. A descriptive analysis will be performed, where medians and interquartile range (IQR) will be used to characterize continuous variables, while frequencies and percentages will be used to summarize categorical data. P-values will be calculated, and less than 0.05 will be deemed statistically significant in all two-sided analyses, where needed, using the Pearson's chi-squared test, Mann-Whitney test, Wilcoxon test, and Mc. Nemar test. Effect size (r) in the Mann-Whitney and Wilcoxon tests will be calculated using the formula r=|Z|/√n ^[14]^. The intervals for small effect, intermediate effect, and strong effect are 0.1 to 0.3, 0.3 to 0.5, and 0.5 and higher, respectively ^[15]^. No interim analysis will be performed because of the short time duration.

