**Methods**

**Study design and setting**

The study will be conducted in two slum areas of Pokhara Metropolitan, Nepal, implementing a quasi-experimental (pre-test-post-test control group) study design involving two groups: intervention (community health worker-led using flipchart and brochure) and control (community information channel led using poster).

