**Data collection**

Data will be collected by trained female data enumerators from a public health background through face-to-face interviews using a structured questionnaire adapted from relevant literature and previous studies on similar topics. The questionnaire covers the basic information of the study subjects, such as age, marital status, education level, and occupation. A total of 14 questions (36 scores) will be asked to assess knowledge about cervical cancer disease itself and its risk factors, and prevention and control measures. Behavior related to cervical cancer screening will be assessed by the utilization of a cervical cancer screening question. Pre-testing of the study tool will be done among 31 women aged 30 to 60 years in a slum area within Ward 29 of Pokhara Metropolitan to ensure its reliability and validity.

A baseline study will be conducted in the selected slum areas to assess the knowledge of cervical cancer and demographic and behavioral characteristics of the participants. Post-test will be done among both the study groups (intervention and control) after the third week and the sixth week.

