**Discussion**

The study aimed to assess the effectiveness of community health workers and community intervention channel interventions in cervical cancer knowledge and screening behavior among women of slum areas in Pokhara Metropolitan, Nepal. We expect that the health education interventions will enhance the knowledge on risk factors, symptoms, prevention and control measures, and screening tests of cervical cancer, along with the increased participation in cervical cancer screening.

Previous studies from Nepal and other countries have found that health education interventions are effective in increasing knowledge and screening of cervical cancer. ^[16–18]^ A study from Nepal reported that female community health volunteers (FCHVs) can play a vital role in achieving the national target of cervical cancer screening.^[16]^ In our study, we will train the women within the slum areas who have a minimum of secondary level education. Although the decision to mobilize participants with a minimum of a secondary level of education was made independently by the researcher and the supervisor, it aligns with the criteria outlined in the revised National Female Community Health Volunteer (FCHV) program strategy of 2019^[11]^. According to the strategy, FCHVs are local community women who serve as a bridge between the community and government health facilities^[11]^. So, we will train 10 participants who have the potential and qualifications to become FCHVs in the future.

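### The planned tests leave the primary between-arm contrast open and adjust for no collected covariate, although the arms are two slums allocated by convenience

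*Protocol*

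**What the plan says.** Under Study design and setting, the Protocol describes a "quasi-experimental (pre-test-post-test control group) study design involving two groups". Under Study participants and sampling procedure, two slums are chosen purposively to be as alike as possible and at similar distance from VIA services. One is then assigned to each arm by convenience; only the enrolment of women within a slum is random. The Discussion part of the Abstract states a comparative aim: CHW-led education against standard community information.

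Under Outcomes: "The primary outcome will be a change in knowledge of cervical cancer". No between-arm contrast is attached to this, and no single time point is named as primary.

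Under Data collection: "The questionnaire covers the basic information of the study subjects, such as age, marital status, education level, and occupation". Both arms are assessed at baseline and again at weeks 3 and 6.

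Under Data Analysis, p-values come from the Pearson "chi-squared test, Mann-Whitney test, Wilcoxon test, and Mc. Nemar test", and a p-value "less than 0.05 will be deemed statistically significant in all two-sided analyses". On magnitude: "Effect size (r) in the Mann-Whitney and Wilcoxon tests will be calculated using the formula r=|Z|/√n". No regression, ANCOVA, difference-in-differences or group-by-time term appears.

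**The concern.** Whole-slum allocation by convenience does not balance the arms even in expectation. The women may differ in knowledge, education or past screening before any education is given. One possible route (an inference, not something the Protocol states) is that the intervention slum has to supply ten women who have passed the SLC, which could favour a better-educated slum. Education is recorded, but no listed test can adjust for it.

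The listed tests also answer different questions. Wilcoxon and McNemar ask whether an arm changed. Mann-Whitney and chi-squared ask whether two arms differ, but on what (follow-up score or change) is not said. The main Discussion section opens with "The study aimed to assess the effectiveness of community health workers and community intervention channel interventions", which makes it easy to read each arm's before-after p-value as evidence of effectiveness. A team following the Protocol to the letter could report a pre-existing slum difference, or a gain seen in both arms, as an effect of CHW education. The Abstract says that results may guide scale-up.

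**Working it through.** **The plan's own figure.** With p1 = 0.73, p2 = 0.87, 1.96 and 0.84: 2.8² × (0.73×0.27 + 0.87×0.13) / 0.14² = 7.84 × 0.3102 / 0.0196 = 124.08 per group. Dividing by 0.80 gives 155.1, stated as 155. The figure reproduces. I use 124 completers per arm below.

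**Assumptions not in the documents.** No true CHW effect; baseline gap d of 0.1 to 0.3 SD between slums; correlation ρ of 0.5 to 0.7 between baseline and follow-up score; normal approximation; two-sided 0.05.

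**1. Follow-up-only comparison, gap regresses.** The expected follow-up difference is ρ×d. Non-centrality = ρ×d×√(124/2) = ρ×d×7.874.

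| d (SD) | ρ | bias (SD) | non-centrality | falsely significant |
|---|---|---|---|---|
| 0.1 | 0.5 | 0.05 | 0.39 | 6.8% |
| 0.1 | 0.7 | 0.07 | 0.55 | 8.5% |
| 0.2 | 0.5 | 0.10 | 0.79 | 12% |
| 0.2 | 0.7 | 0.14 | 1.10 | 20% |
| 0.3 | 0.5 | 0.15 | 1.18 | 22% |
| 0.3 | 0.7 | 0.21 | 1.65 | 38% |

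**2. The same comparison, gap stable.** In a simulation of 1,500 runs per setting, Mann-Whitney at follow-up was significant in about 33–35% of runs at 0.2 SD and 61–64% at 0.3 SD.

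**3. Mann-Whitney on individual change scores, gap stable.** In the same simulation it was significant in about 4–6.5% of runs in every setting, including those with a retest gain of 0.3 SD shared by both arms. This use fits the listed tests.

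**4. Within-arm test under a shared retest gain.** For an assumed gain of 0.25 SD, z = 0.25/√(2(1−ρ)) × √124. At ρ = 0.5, z = 2.78 and the test is significant 79.5% of the time. At ρ = 0.7, z = 3.59 and the figure is 94.9%. This applies to each arm, posters included.

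**5. Which adjusted contrast?**
- *ANCOVA on baseline, stable gap:* bias is (1−ρ)d and residual SD is √(1−ρ²). At d = 0.3 and ρ = 0.5: 0.15/0.866 × 7.874 = 1.36, about 28% falsely significant. At ρ = 0.7: 0.09/0.714 × 7.874 = 0.99, about 17%.
- *Difference in change, regressing gap:* bias has the same size with opposite sign, and the SD of change is √(2(1−ρ)). At d = 0.3 and ρ = 0.5: 0.15/1 × 7.874 = 1.18, about 22%. At ρ = 0.7: 0.09/0.775 × 7.874 = 0.91, about 15%.

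Each is unbiased under the assumption that biases the other.

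**6. Screening uptake.** Starting from the planning value of 73%, a pre-existing gap of 5, 10 or 14 percentage points that persists to follow-up makes a follow-up chi-squared test significant in about 15%, 48% or 79% of trials with 124 per arm.

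**The case against.** Four points can fairly be made in the Protocol's favour.

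- *Baseline can be handled within the list.* A reader might infer that none of the planned tests can take baseline knowledge into account. The documents do not support that. The primary outcome is a change, the design is pre-test/post-test with a control group, and Mann-Whitney on change scores subtracts baseline. It holds near 5% under a stable gap. What stands against the Protocol is that it does not say this is the contrast, and that even this test ignores the demographics.
- *Retesting cancels.* A reader might infer that giving the same questionnaire three times inflates the comparison of arms. A gain common to both arms cancels in any between-arm test. It misleads only if within-arm results are read as superiority over posters, and the Protocol nowhere says that they will be.
- *The slums are matched.* This is a real safeguard, and it makes a large gap less likely. But the only matching variable named is distance to VIA services. Similar access does not ensure similar knowledge, education or past screening.
- *Detail belongs in an analysis plan.* No statistical analysis plan is shown. Confidence intervals and the exact covariate list are commonly left to one, so their absence alone is no fault. The unsigned r is minor too, because medians will show direction. However, the Protocol does fix the list of tests, and that list contains no adjusted analysis.

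**Conclusion.** The point holds in this form: the Protocol does not fix which contrast answers its comparative question, and the tests that it does fix allow no covariate adjustment in a non-randomised comparison of two slums. A sound reading (change scores compared between arms) is permitted, but so are unsound ones, and the choice stays open after the data are seen.

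For a follow-up-only comparison, the false-positive rate is about 7% to 38% instead of 5%, for gaps of 0.1 to 0.3 SD that regress, and higher if the gap is stable. The gap, the correlation and the regression of the gap are assumptions; the documents give no value for any of them. The lower end, about 7–9% at 0.1 SD, is what good matching might achieve.

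These figures do not show that the trial will reach a false conclusion. Nor does ANCOVA alone repair the problem, since it is biased when the gap is stable. With one slum per arm, no individual-level adjustment can separate CHW education from whatever else differs between the two slums.

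**What to change.** Amend the Data Analysis section as follows.

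1. Name one primary contrast: the difference between arms in change in knowledge score from baseline to week 6 (difference-in-differences or a group-by-time term), adjusted for age, education, marital status and occupation. Report it in points on the 36-point scale with a 95% CI.
2. Give ANCOVA on the baseline score, with the same covariates, as a sensitivity analysis. Say why: the two analyses differ in whether the slum gap is taken to be stable or to regress.
3. For screening uptake, use a logistic model that includes baseline screening status and the same demographics.
4. Keep Wilcoxon and McNemar as descriptive, and state that their p-values are not evidence that CHW education does better than posters.
5. State as a limitation that, with one slum per arm, no adjustment separates the intervention from slum-level effects, and that the CI does not cover that uncertainty.

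The cost is small: one rewritten section and slightly more analysis work. The demographics, baseline knowledge score and screening behaviour are already to be collected, and no extra participants are needed. The downside is reliance on model assumptions for a bounded 36-point score, which should be checked.

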**Figure 1: Study process (flow diagram)**

**Sample size calculation**

The sample size was calculated using screening rate at baseline study=73% (p1), the expected change in proportion up to 87% (p2), ^[13]^ with other values conventionally, as Z_a/2_=1.96 (for 95% CL), Z_β_=0.84 (β=80%), and using the formula for sample size (n)=[(Z_a/2_+ Z_β_)^2^. (p1(1-p1)+p2 (1-p2))]/(p1-p2)^2, we obtained 124.08 for each group. With an attrition rate of 20%, the final sample size for each group will be 155.

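### If outcomes differ by CHW, the planned tests, which treat women as independent, give P-values that are too small in the CHW arm and between arms

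*Protocol*

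**What the plan says.** The Intervention section describes delivery by a small group of lay educators: "Ten participants who had at least passed the SLC will be enrolled as community health workers (CHWs) in the intervention group". They receive one common four-hour training, and then "CHWs will reach the doors of the participants to provide health education on cervical cancer" with flip charts and brochures. Contact is individual and single: "CHWS will visit the participants just once for an education session, which will take 15 minutes for each participant". The comparison arm has no educator: "In the control group, posters will be displayed in two different locations after the baseline study".

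The Sample size calculation section arrives at 124.08 women per group, and then states: "With an attrition rate of 20%, the final sample size for each group will be 155".

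The Data Analysis section lists the tests as Pearson's "chi-squared test, Mann-Whitney test, Wilcoxon test, and Mc. Nemar test" and sets the threshold: "less than 0.05 will be deemed statistically significant in all two-sided analyses". Neither section mentions an educator effect, an ICC, a design effect, a clustered variance or a mixed model. The protocol does not say how women are shared among the CHWs, or whether the CHW who taught each woman is recorded.

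**The concern.** Women taught by the same CHW share that person's accuracy, skill and manner. If CHWs differ in these, the knowledge scores (the primary outcome) and the screening behaviour of their women are correlated. The Wilcoxon and McNemar tests allow for pairing within a woman, but none of the four tests allows for correlation between women. The effective sample in the CHW arm is then smaller than the tests assume, and the standard error is understated.

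Two kinds of test are exposed: between-arm comparisons after the intervention, and pre-post tests within the CHW arm. Baseline comparisons and pre-post tests within the poster arm are not affected. What is at stake is that a few good or poor CHWs could produce a significant result that is then read as a property of CHW education in general. The abstract's discussion hopes that the results may guide scalable programmes, and that means other CHWs.

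**Working it through.** **The plan's own figure.** Inputs from the Sample size calculation section: p1 = 0.73, p2 = 0.87, z-values 1.96 and 0.84.

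n = (1.96 + 0.84)² × (0.73 × 0.27 + 0.87 × 0.13) / 0.14² = 7.84 × (0.1971 + 0.1131) / 0.0196 = 124.08, and 124.08 / 0.80 = 155.1. Both stated figures reproduce. The formula contains no design effect.

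**Women per CHW.** 155 / 10 = 15.5; 145 / 10 = 14.5 if the ten CHWs are themselves among the 155; 124 / 10 = 12.4 after 20% attrition. Equal caseloads are assumed. Unequal ones would make the inflation larger.

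**Formulas.** Clustering is in the CHW arm only, with m = 12.4.
- Design effect in the CHW arm: DE = 1 + (m − 1) × ICC.
- Under no effect the arms have equal variances, so the variance of the between-arm difference is inflated by F = (1 + DE) / 2.
- True between-arm error = 2 × [1 − Φ(1.96 / √F)].
- True error of a pre-post test within the CHW arm = 2 × [1 − Φ(1.96 / √DE)], if the same ICC holds for change scores.
- Power for screening uses the protocol's two variances and inflates only the CHW arm: Φ(0.14 / √[(0.1971 + 0.1131 × DE) / 124] − 1.96).

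**Example, ICC 0.05.** DE = 1 + 11.4 × 0.05 = 1.57; F = 1.285; 1.96 / √1.285 = 1.729, so the error is 8.4%. Power: 0.1131 × 1.57 = 0.1776; √[(0.1971 + 0.1776) / 124] = 0.0550; 0.14 / 0.0550 − 1.96 ≈ 0.59, so power is 72%.

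| Assumed ICC | DE | F | Between-arm error | Simulated Mann-Whitney | Power, screening | Within-CHW-arm error | Simulated Wilcoxon |
|---|---|---|---|---|---|---|---|
| 0 | 1.00 | 1.00 | 5.0% | 4.9% | 80% | 5.0% | 5.5% |
| 0.01 | 1.11 | 1.06 | 5.7% | 5.2% | 78% | 6.3% | 6.3% |
| 0.02 | 1.23 | 1.11 | 6.3% | 6.1% | 77% | 7.7% | 7.5% |
| 0.05 | 1.57 | 1.285 | 8.4% | 8.6% | 72% | 11.8% | 11.2% |
| 0.10 | 2.14 | 1.57 | 11.8% | 11.0% | 65% | 18.0% | 16.5% |

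The simulations used ten CHWs with 12 or 13 women each, 124 independent controls, normal data and no mean effect (10,000 runs for Mann-Whitney, 4,000 for Wilcoxon). They agree with the formulas, except that the within-arm formula runs slightly high at the larger ICCs.

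Without attrition (15.5 women per CHW) the between-arm error is 5.8% / 6.7% / 9.3% / 13.6% for ICC 0.01 / 0.02 / 0.05 / 0.10.

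**The case against.** **No ICC is given.** A reader might infer that the P-values are certainly too small. The documents do not support that: it needs an educator ICC above zero, and none is stated. A common training, standard flip charts and brochures, and a single short session may all limit differences between CHWs. At ICC 0.01 the between-arm error is only 5.7%. This stands, so the point is conditional.

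**Caseload is inferred.** The protocol gives no number of women per CHW and does not state that each woman sees only one CHW. This also stands.

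**Power.** A reader might apply the equal-variance factor √F to the stated 80% and infer 76% / 70% / 61% at ICC 0.02 / 0.05 / 0.10. The protocol's own rates do not support that. The inflated arm is the one at 87%, which has the smaller variance, and the loss is to 77% / 72% / 65%. These figures precede any small-sample correction, which would lower them somewhat. They concern screening; the protocol states no power for knowledge.

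**Within-arm tests.** Their figures need the further assumption about change scores, and such tests do not compare CHW education with posters. This stands as a caveat.

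**Slum and arm are confounded.** Each arm is one conveniently assigned slum area. A reader might infer that allowing for CHW makes the between-arm test valid. It does not, because between-slum variance cannot be estimated from one area per arm. Educator clustering is the lesser problem, but unlike the slum effect it can be estimated, since there are ten CHWs.

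**Target of inference.** A random CHW effect is needed only if results are meant to reach beyond these ten women. The protocol says no more than that results may guide scalable programmes, but that is an inference to other CHWs.

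**Left to an analysis plan.** A separate plan may exist. The protocol itself, however, names the tests and the threshold, so this is a stated choice and not a gap.

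**Conclusion.** The concern holds in conditional form. The delivery described under Intervention creates educator groups in one arm, and the tests fixed under Data Analysis ignore them. If outcomes differ by CHW, nominal 5% between-arm tests after the intervention have a true error between about 5.7% (ICC 0.01) and 11.8% (ICC 0.10), and power for screening falls to between about 78% and 65%. Within the CHW arm the error is about 6% to 18%, but only if the same ICC applies to change scores.

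These figures rest on an assumed ICC range, equal caseloads of 12.4 analysed women, one CHW per woman and, for power, the protocol's 73% and 87%. The effect is small at the bottom of the range and material from about 0.05. It is secondary to the one-slum-per-arm confounding, but it can be repaired cheaply if the CHW is recorded at the visit and may not be recoverable afterwards.

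**What to change.** 1. Record for each woman, on the visit form, which CHW gave the session.
2. In Data Analysis, make the between-arm analyses and those within the CHW arm allow for CHW. For knowledge, use a linear mixed model with a random CHW effect in the intervention arm only (a partially nested model). For screening, use standard errors clustered on CHW, with each control woman as her own cluster. Apply a small-sample correction, as there are only ten clusters.
3. Keep the rank tests as a supporting analysis if wished.
4. State that this corrects the educator level only, and that with one slum area per arm the between-arm P-value still cannot separate the intervention from slum differences.

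Random allotment of women to CHWs is not required for this fix; it would change the fieldwork.

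**Cost.** One extra form field, a model in place of a rank test as the main analysis of a 36-point score, and wider confidence intervals: about 13% at ICC 0.05 with equal variances (√1.285 = 1.13), before the small-sample correction.

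### The protocol grades the knowledge effect only by an unsigned r with n undefined for paired data, and the labels also apply to within-slum change, where they say nothing about CHW visit versus poster

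*Protocol*

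**What the plan says.** The primary outcome is change in knowledge (Protocol, Outcomes). The instrument is described under Data collection: "A total of 14 questions (36 scores) will be asked to assess knowledge about cervical cancer disease itself". Both slums are assessed at baseline, week 3 and week 6.

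Data Analysis lists Mann-Whitney and Wilcoxon tests, with a two-sided 5% significance level. It does not say which test serves which comparison. On effect size it states: "Effect size (r) in the Mann-Whitney and Wilcoxon tests will be calculated using the formula r=|Z|/√n". The grading is: "The intervals for small effect, intermediate effect, and strong effect are 0.1 to 0.3, 0.3 to 0.5, and 0.5 and higher, respectively". The formula and the bands are given for both tests without distinction, and n is not defined. The same section plans medians and IQRs for continuous variables. It names no between-arm difference in score points and no confidence interval. The protocol gives no SD for the knowledge score or its change.

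**The concern.** The study compares a CHW home visit with posters, so the quantity of interest is how much more knowledge was gained in one slum than in the other. The only graded measure differs from that in four ways.

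- The absolute value removes direction, so a result favouring the poster gets the same label as an equal one favouring the visit.
- r is a rescaled test statistic. It depends on the ratio of gain to SD, not on points out of 36.
- For paired data, n can be the number of women or the number of measurements. With this left open, the label can depend on a choice made after the data are seen.
- The bands cover the within-slum Wilcoxon test. Repeating the same questionnaire, or the posters themselves, could raise scores in the control slum and earn a label there. The Discussion section frames the aim as assessing both interventions, which makes it easy to read a within-slum label as evidence of effectiveness.

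**Working it through.** **1. The plan's own figure.** The sample size uses p1 = 0.73, p2 = 0.87, and Z values of 1.96 and 0.84: (1.96 + 0.84)² × (0.73×0.27 + 0.87×0.13) / 0.14² = 7.84 × 0.3102 / 0.0196 = 124.08. Dividing by 0.80 gives 155.1. Both match the stated 124.08 and 155. The calculation is for screening uptake, so it supplies no knowledge SD. The SD below is therefore an assumption, shown over a range.

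**2. What n does to r.** Each pair has two observations, so r with n = observations equals r with n = pairs divided by √2 = 1.41. A pairs-based r between 0.50 and 0.707 falls from strong to intermediate. One between 0.30 and 0.424 falls from intermediate to small. If all 124 women gain, with no ties, Z = (124×125/4) / √(124×125×249/24) = 3875 / 401.0 = 9.66. The ceiling for r is then 9.66/√124 = 0.87 (pairs) or 9.66/√248 = 0.61 (observations).

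**3. Size of r for a 2-point shift** (2/36 = 5.6% of the scale). Large-sample values under a normal shift model, with δ the shift:

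- Wilcoxon, n = pairs: r = √3 × [Φ(√2·δ/SD of change) − 0.5]
- Wilcoxon, n = observations: the same divided by √2
- Mann-Whitney, equal groups, n = all women compared: r = √3 × [Φ(δ/(√2·SD)) − 0.5]

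Example at SD 3, n = pairs: √3 × [Φ(0.943) − 0.5] = 0.57.

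| Assumed SD | Wilcoxon, pairs | Wilcoxon, observations | Mann-Whitney |
|---|---|---|---|
| 2 | 0.73 strong | 0.52 strong | 0.45 intermediate |
| 3 | 0.57 strong | 0.40 intermediate | 0.31 intermediate |
| 3.5 | 0.50 strong | 0.36 intermediate | 0.27 small |
| 4 | 0.45 intermediate | 0.32 intermediate | 0.24 small |
| 5 | 0.37 intermediate | 0.26 small | 0.19 small |
| 6 | 0.31 intermediate | 0.22 small | 0.16 small |

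**4. Where r reaches 0.5.** Solving for r = 0.5:

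- Wilcoxon, pairs: gain = 0.567 × SD of change, so 2 points needs SD ≤ 2/0.567 = 3.5.
- Wilcoxon, observations: gain = 0.94 × SD of change, so SD ≤ 2/0.94 = 2.1.
- Mann-Whitney: difference = 1.134 × SD, so SD ≤ 2/1.134 = 1.8.

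At SD 5, the Wilcoxon test needs about 2.8 points (pairs) or 4.7 points (observations) for a strong label.

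**5. Simulation check.** With whole-point scores, tie correction, 155 women per slum and 2000 runs, the chance that a 2-point mean gain earns a strong within-slum label (n = pairs) is 0.87 at SD 3, 0.54 at 3.5, 0.21 at 4 and 0.03 at 5. A mean loss of 2 points gives the same r as a gain of 2.

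**The case against.** The formula and its bands are cited conventions, and any standardised effect size depends on the SD. The protocol ties significance to P < 0.05 and sets no success rule on a label. A statistical analysis plan may exist that defines n and adds an estimate with an interval. All of this is fair and keeps the point minor. It does not remove the labels that the protocol itself attaches to within-slum tests, nor the missing sign.

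Three stronger readings are tempting, and the document does not support them.

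- A reader might infer that a gain of about 2 points will be called strong. That needs both n = pairs and an SD of change of about 3.5 or less, and the protocol states neither.
- A reader might infer that points and direction will be invisible. Medians and IQRs are planned and will show both descriptively. The sign is lost from r, not from the report. Still, arm-wise medians are not a between-arm difference in change, and they carry no measure of its uncertainty.
- A reader might infer that equal gains in both slums would pass as a CHW effect. If the slums did not differ in change, a Mann-Whitney test of change would give r near 0 and expose this.

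It would also be too strong to say that the Wilcoxon r ignores how much women learned: the signed-rank statistic ranks the sizes of the changes, and r rises with gain relative to SD.

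**Conclusion.** The point holds as a cheap improvement to a stated method. It is not an error in any stated number. Three faults need no assumed SD: r is unsigned, n is undefined for paired data (a factor of 1.41), and the labels extend to within-slum change, where they say nothing about CHW visit versus poster. The practical size rests on an assumed SD and a normal shift model: a 2-point gain within a slum, the control slum included, ranges from strong (SD of change up to about 3.5, n = pairs) to small (SD of change 5 or 6, n = observations). Severity is minor, because what is affected is the interpretation of the primary outcome, not the validity of the tests.

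**What to change.** In Data Analysis:

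- State the primary effect as the between-arm difference in change in knowledge score, intervention minus control, in points out of 36, with a 95% confidence interval. A Hodges-Lehmann estimate fits the Mann-Whitney test.
- Keep r and its labels only for the between-arm Mann-Whitney comparison, with its sign and with n defined as all women compared.
- Drop the labels for the within-arm Wilcoxon tests.

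The cost is about two sentences and one extra output, with no new data and no change to the design. The downside is that a strong label for within-arm change is no longer available.
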